### Intervention

Both the intervention and control groups were given SSRI antidepressants and antidepressant psychotherapy. The control group was given conventional care, and the intervention group was given 6 weeks of PEERS intervention on top of conventional care. The intervention is delivered by a senior psychosomatic practitioner and a psychology teacher who provides verbal instructions, prompts, feedback, and assistance when needed.

The intervention will be carried out by members of the research team, who will be trained in relevant psychological knowledge and specific intervention methods, and will be assessed on their knowledge of depression and anxiety, the process of PEERS training, the details of implementation and precautions, etc.

### The controlled group

The control group will be given routine care based on normal administration of SSRI antidepressants and antidepressant psychotherapy (see Table 1 for details).

**TABLE 1 T1:** Content of conventional nursing.

① Daily care	Assisting patients with daily care such as eating, hygiene, toileting, and sleeping
② Psychological care	For example, we understand in detail the causes of depression and related illnesses and take personalized care measures to guide patients to face illnesses and setbacks positively and happily.
③ Environmental care	Provide patients with a quiet and suitable care environment, keep the air in the room pleasant, open the windows for ventilation every day, practice gentle care, create suitable sleeping conditions for patients and keep them in a happy mood
④ Medication care	Observe drug efficacy and adverse effects when using SSRI antidepressants as prescribed by your doctor and provide timely feedback
⑤ Health education	Provide guidance on daily living skills, vocational skills, and social skills

### Intervention group

The intervention group implemented the PEERS training intervention (see Table 2 for details) on top of the normal administration of SSRI antidepressants and antidepressant psychotherapy and routine care, using different social themes to intervene with a fixed frequency for the patients, twice a week for 6 weeks. Each lesson uses a Socratic questioning approach to introduce questions to promote engagement with young depressed patients. Each lesson consists of four sessions, and the first session starts with feedback of the last assignment (8 min); the second session is a didactic presentation and teaching exercise led by the trainer (25–30 min); the third session is a rehearsal of the behavior by the participants themselves (10–20 min). The fourth session assigns socialization homework (2 min) to each patient, which is required to be completed at the end of the session to consolidate and improve on what has been learned in class.

**TABLE 2 T2:** Course arrangement.

**Lesson**	**Intervention themes**	**Outline**	**Duration and frequency of intervention**
Lesson 1	Exchange of information and two-way communication to develop social networks	To communicate with each other by exploring the same interests and then forming a social network with like-minded people	Two lessons per week (one lesson per week in lesson 9/10), 45–60°min each
Lesson 2	Appropriate use of humor	Having a positive and optimistic mindset and learning the basic rules of appropriate humor	
Lesson 3	Small group strategy: Entry and exit	Assessing the acceptance of the small group you want to join, learn how to join the conversation with other young people and learn what to do when attempts fail	
Lesson 4	Interactive activities	How to organize and execute an in-house party and how to prepare, plan and execute an event well.	
Lesson 5	Good sporting spirit	How to perform well in video games, board games, sports, and other competitions	
Lesson 6	Handling ridicule	Counteracting through appropriate behavior to deal with unintentional verbal teasing from others	
Lesson 7	Dealing with bullying and changing a bad reputation	Includes long-term strategies for dealing with cyber violence, real-life bullying (e.g., physical threats) and changing a bad reputation	
Lesson 8	Resolving disagreements and arguments with friends	Specific steps to take when there is a disagreement or conflict with a friend	
Lesson 9	Dealing with rumors and gossip	Includes behavioral strategies to minimize the harm caused by gossip	
Lesson 10	Knowledge summary and review	A review of the social skills and knowledge learned and a graduation ceremony to round off the training.	

### Assignment of intervention

Prior to the start of the intervention, different ward were randomly divided into intervention and control groups using a coin toss by an investigator not involved in the implementation of the intervention to prevent contamination, and eligible subjects were sought within the respective ward.

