## Materials and methods and analysis

### Study design

This study protocol conforms to the Standard Protocol Items: Recommendations for Interventional Trials (SPIRIT) guidelines (see Additional file 1) and accords with the SPIRIT Figure (Figure 1). The proposed PEERS training for the trial is based on literature research and expert discussion and is an optimized update of the original PEERS training program. Participant engagement in the trial will be divided into two phases, a non-intervention phase before randomization and an intervention phase 6 weeks after randomization. This trial was designed to validate the efficacy of the localized PEERS training, and therefore the control group in this trial will not receive any interventions other than usual care. Participants will be randomized by ward to receive the intervention, and due to the specific nature of the intervention, blinding will not apply to the interventionists, and the study will remain blind to scale assessors and data entry only.

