### Inclusion criteria

① Aged 18–28°year (45).

② Willing and able to give informed consent.

③ The patient meets the diagnostic criteria for depression of the International Statistical Classification of Diseases and Related Health Problems 10th Revision (ICD-10) and gets HAMD-17 (≥ 18 points) and without other comorbid psychiatric disorders and two or more associate or chief physicians diagnosed with depression.

④ Patient has some degree of social impairment (LSAS ≥ 16 points).

⑤ Normal intelligence, without severe speech or emotional expression disorders.

⑥ Patients using SSRI antidepressants.

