### Outcome measure

The measurement of each scale measure, the outcome indicators will all be carried out by investigators who are not involved in the implementation of the intervention.

A baseline survey will be conducted by the investigator after the study subjects are identified, and basic information will be collected on the subjects, including age, gender, marital status, mode of payment (self-pay, agricultural insurance, medical insurance, and others), type of depression (general depressive disorder, anxiety depressive disorder, and others), previous history, family history, duration of illness and medication use, etc.

Considering that the first onset of action of antidepressants is between 2 and 4°weeks (46), We, therefore, chose to collect the subjects’ depression scores at three-time points: baseline, week 3 of the intervention and week 6 of the intervention. The scales were selected based on clinical applicability and reliability to dynamically assess the efficacy of the localized PEERS training.

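### Wards are allocated before patients are sought and nobody who enrols patients is masked, so the arms can differ by selection; the Study design section implies the opposite order.

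*Protocol article*

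**What the plan says.** Assignment of intervention states that "different ward were randomly divided into intervention and control groups using a coin toss", done by an investigator who does not deliver the intervention and justified by the wish to avoid contamination. The same sentence ends "and eligible subjects were sought within the respective ward". Study design confirms the unit: "Participants will be randomized by ward to receive the intervention".

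On masking, Study design says that "the study will remain blind to scale assessors and data entry only". Outcome measure and Statistical data collection add that the scales are administered by people who do not deliver the intervention.

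On entry, Inclusion criteria require HAMD-17 of at least 18, LSAS of at least 16, normal intelligence, no severe speech or emotional expression disorder, and that "two or more associate or chief physicians diagnosed with depression". Consent is individual (Participants; Ethics and dissemination). On baseline, Outcome measure says: "A baseline survey will be conducted by the investigator after the study subjects are identified".

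On sequence, Study design splits each participant's involvement into "a non-intervention phase before randomization and an intervention phase 6 weeks after randomization".

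**The concern.** When clusters are allocated first and individuals are recruited afterwards, randomization protects the comparison of wards but not the choice of patients within them. Anyone who knows that a ward runs PEERS can, without intending to, approach the more motivated or more promising patients there, or apply a judgement-based criterion more or less strictly. The two groups then differ before treatment starts, and part of the LSAS difference may be selection that is read as a PEERS effect.

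The safeguards that the article states lie elsewhere. Separating the coin tosser from delivery protects the toss. Masking assessors and data entry protects measurement. Neither covers the step between allocation and enrolment.

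The conflict about sequence matters in its own right. If participants pass through a phase before randomization, enrolment could be free of knowledge of the arm. If they are sought only in wards already allocated, it need not be. A reader cannot tell which will be followed.

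**Working it through.** The article gives no figure for this point, so the check is mainly a comparison of sections.

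1. **Order.** Assignment of intervention names the division of wards first and the search for eligible patients second, in the *respective* ward. The sentence says only that allocation precedes the start of the intervention, but its natural reading is wards first, patients second.
2. **Consequence.** Allocation is by ward, so a patient's arm equals the ward's arm. On this order it is fixed before approach, eligibility assessment and consent. Baseline follows identification of the patient, so it too comes after allocation.
3. **Who could know.** The masked set is scale assessors and data entry. Diagnosing physicians and whoever approaches and enrols are not in it, and the article does not say who recruits. A ward in which PEERS lessons run about twice a week (Intervention group) is recognisable as an intervention ward. That recruiters *can* know the arm is therefore a well-supported inference. That they *do* know is not stated.
4. **Room for selection.** The scale cut-offs are scored by masked or non-intervention staff. The diagnosis, the judgements on intelligence and emotional expression, and the decision whom to approach are not covered by any stated masking.
5. **Contradiction.** Study design has participants engaged before randomization. Under step 1 there are no participants until wards have been randomized. Both cannot describe the same trial.
6. **Timing words.** The Abstract counts weeks from randomization. Outcome measure, Primary outcome and Secondary outcome count weeks of the intervention. Participants gives recruitment as July 2022 to January 2023. If wards are allocated before that, weeks since randomization is not an individual patient's clock. The outcome sections are workable, and the Abstract needs to match them.

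**Illustration only, not an estimate.** Inputs from Sample size: variance 243.04, so SD = √243.04 = 15.59; 62 patients before the allowance for loss, so 31 per arm. Assumptions: no true effect, independent patients, a two-sided 5% test of week-6 LSAS without baseline adjustment, and a selection-induced difference of b points present at week 6.

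SE = 15.59 × √(2/31) = 3.96.

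False-positive rate = 1 − Φ(1.96 − b/SE) + Φ(−1.96 − b/SE).

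| Assumed b (LSAS points) | b/SE | False-positive rate |
|---|---|---|
| 0 | 0 | 5% |
| 2 | 0.51 | 8% |
| 4 | 1.01 | 17% |
| 6 | 1.52 | 33% |
| 8 | 2.02 | 52% |

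The document supports no particular row.

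**The case against.** The strongest defence has four parts.

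- **Ward allocation is deliberate.** It is chosen to prevent contamination, and with inpatients admitted over months, consent before allocation cannot cover everyone. This stands. The point is not against ward allocation, and it is why the fix treats later admissions separately.
- **Scoring is protected.** Scales are scored by masked or non-intervention staff, with the same cut-offs in both arms. This stands too. A reader might infer that HAMD-17 and LSAS eligibility are scored with the arm known, or that patients consent knowing what their ward offers. The article says neither. The gap concerns diagnosis, approach and enrolment.
- **The analysis may absorb baseline severity.** The Abstract speaks of change from baseline, and Statistical methods foresees an intervention-by-time interaction. If baseline is one of the time levels, a constant shift in LSAS does not create an interaction. This stands in part. Statistical methods names week 3 and week 6 scores, and no version of the analysis removes selection on unmeasured prognosis or motivation.
- **An article omits operational detail.** Recruiter masking and screening logs may be in a full protocol. Fair, but the article does state an order of events, and states it in two incompatible ways.

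Two stronger readings are tempting and unsupported. First, a reader might take the pilot's baseline LSAS gap (55.50 v 52.25 in Table 3) as a sign or yardstick of selection. The PEERS group was the worse one, contrary to selection of less ill patients; the Discussion says that the pilot was randomized; and with six per group the standard error is √((21.20² + 20.30²)/6) = 12.0, so a gap of 3.25 is noise. Second, a reader might infer that separate tosses could put every ward in one arm. The article states neither the number of wards nor a toss for each, and its wording also fits one toss that divides the wards. Nor is 37 per arm a property of the toss: it is a recruitment target.

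**Conclusion.** The point holds as a risk in the design as written, together with a contradiction between two sections. Wards are allocated before patients are sought, no one who diagnoses, approaches or enrols is masked, and Study design describes a participant phase before randomization that this order rules out. The primary LSAS comparison is therefore open to selection.

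Its size is unknown. The illustration shows only that a lasting difference of a few LSAS points would matter at this sample size, under its stated assumptions. It does not show that such a difference exists or which arm it would favour.

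The conclusion rests on the natural reading of the allocation sentence and on the inference that ward status is recognisable to staff. If the full protocol shows that patients were screened and consented before the toss, or that recruiters were masked, only the inconsistent wording remains.

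**What to change.** 1. Reconcile Study design with Assignment of intervention, so that one order of allocation, identification, consent and baseline is stated.
2. For patients already on the wards, screen, consent and take baseline before the allocation is drawn.
3. For later admissions, screen all consecutive admissions in every ward. Have the existing blinded, non-intervention assessors score HAMD-17 and LSAS and record eligibility before the ward's arm is disclosed to the patient. Log numbers eligible, approached, refused and enrolled by ward.
4. State that ward allocation is a single draw that places wards in both arms.
5. Align the Abstract's timing from randomization with the weeks of intervention used in the outcome sections.

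If recruitment is already under way, items 1 and 5, a log from now on, and open reporting of the order actually followed remain possible.

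The cost is protocol wording, a screening log and slightly slower enrolment, with no extra staff. For later admissions the log and consecutive screening limit selection and make it visible. They cannot exclude it, because staff may still know the ward's arm.

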### Outcome measure

The measurement of each scale measure, the outcome indicators will all be carried out by investigators who are not involved in the implementation of the intervention.

A baseline survey will be conducted by the investigator after the study subjects are identified, and basic information will be collected on the subjects, including age, gender, marital status, mode of payment (self-pay, agricultural insurance, medical insurance, and others), type of depression (general depressive disorder, anxiety depressive disorder, and others), previous history, family history, duration of illness and medication use, etc.

Considering that the first onset of action of antidepressants is between 2 and 4°weeks (46), We, therefore, chose to collect the subjects’ depression scores at three-time points: baseline, week 3 of the intervention and week 6 of the intervention. The scales were selected based on clinical applicability and reliability to dynamically assess the efficacy of the localized PEERS training.

### Primary outcome

Liebowitz social anxiety (LSAS) at week 3 and week 6 of the intervention will be assessed to measure social anxiety.

The LSAS scale was developed by Liebowitz in 1987 (47). It is commonly used to assess subjects’ social anxiety and is one of the most commonly used scales to provide a good picture of a subject’s social situation. The 24-item scale assesses fear in 11 social and 13 operational contexts. Scored on a four-point scale, for the fear subscale: 0 (none); 1 (mild), tolerable; 2 (moderate), distressing; 3 (severe), seriously interferes with daily life and work. For the avoidance subscale: 0 (never), 1 (occasionally), 2 (often), 3 (always). The final scores are added together, and the higher the total score, the more severe the social anxiety state. Mild anxiety is defined as a total score of less than 16, while severe anxiety is defined as a score of more than 60 (48). The Chinese version of the LSAS was tested for reliability and validity, and the Correlation between the items and the total score was good, the Cronbach’s α coefficient of each subscale was greater than 0.9, and the total scale score of the retest reliability was 0.779, the scale was generally satisfactory (49).

### Secondary outcome

①Rate of decline in severe social anxiety: A comparison will be made between the number of people in the intervention group and the control group with a decrease in severe anxiety as a percentage of the original number after week 6 to visually demonstrate the efficacy of PEERS training.②Social avoidance and distress (SAD) scale: Compilated by WATSON et al. in 1969 (50), it contains 28 entries. The scale is a “yes-no” scale that assesses the tendency to avoid social interaction and subjective feelings of distress. The higher the patient’s score, the more severe the social avoidance and distress. The mean correlation index of the Chinese version of the SAD total score is greater than 0.75. The internal consistency reliability of the SAD total scale is greater than 0.85, and the avoidance and distress subscales are both above 0.72, which is generally satisfactory (51). Subjects will be administered questionnaires before the intervention, at week 3 of the intervention and at week 6 of the intervention to compare changes in social fear.③Social self-efficacy scale (PSSE) scale: Compilated by Smith and Betz in 2000 (52). The scale is a one-factor structured questionnaire developed for adults and university students, with 25 questions on a five-point scale from 1 to 5, with one being “not at all confident” and five being “completely confident.” The questionnaire covers six sections of social interaction, covering all aspects of social situations. The reliability coefficient of the Chinese version of the PSSE scale is above 0.92, with good construct validity; the Cronbach’s α coefficient is 0.90, indicating good internal consistency (53). Subjects will be administered questionnaires before the intervention, at week 3 of the intervention and at week 6 of the intervention to compare changes in social self-efficacy.④Hamilton depression scale (HAMD-17) scale: Developed by Hamilton in 1960, it is the most commonly used questionnaire for assessing depression in hospitals (54). Most of the HAMD-17 entries are scored on a five-point scale from 0 to 4. The scale is applied to adult patients with depressive symptoms, and the patient’s condition is assessed over a period of nearly one week. The total score is the sum of the factor scores; the higher the score, the more severe the condition. A total score of more than 24 may indicate severe depression, a score of more than 17 may indicate moderate depression, and a score of less than seven may indicate that the patient is not depressed. In a Chinese version of the HAMD-17 with 329 patients with depression, the inter-rater agreement met the criteria (Pan-kappa = 0.92), and the corresponding coefficient for internal consistency was 0.714, making the Chinese version of the scale very satisfactory (55). Subjects will be administered questionnaires before the intervention, at week 3 of the intervention and at week 6 of the intervention to compare changes in depressive symptoms.

### Sample size

#### Preliminary experiments

The purpose of the initial pre-experiment was to test the feasibility of the optimized PEERS training program in a young adult with depression. We included 12 young adults with depression, six in the intervention group and six in the control group. The intervention group used the PEERS to pre-experiment with the patients for a period of 6 weeks, following a lesson plan that closely followed the four components of feedback on assignments, didactic presentations, didactic exercises and structured training, and the control group had no intervention.

#### Official experiment

This trial is a clinical intervention study, and the primary outcome indicator is the LSAS score. Compare sample size formulae based on means $n=\frac{2^{2}\,{\left(\mu_{\alpha }+\mu_{\beta }\right)}^{2}\,\sigma^{2}}{\delta^{2}}$. Take α = 0.05, β = 0.10. From the pre-test, we can calculate that σ2 = 243.04 and δ2 = 272.25, estimating a sample size of about 62 cases, and considering a 20% missed visit, 62 + 62*0.2 = 74, 74 patients are to be included in the formal trial, 37 in the intervention group and 37 in the control group.

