The design of the experiment took into account the possibility of changes in the subject’s condition, and thus we set a 20% lost visit to ensure an adequate sample size. The intervention course is arranged in four interlocking sessions to refresh the knowledge taught and apply it to practice, while arranging for the coaches to take the lead and ensure the course is conducted properly, but more so to encourage the hands-on practice by the patients, using the class as an opportunity for patients to communicate and learn from each other, promoting their understanding of each other and helping each other to practice their social skills.

Before the formal trial began, a pre-experiment was conducted to examine both the motivation and cooperation of the study subjects. At the same time, the content of the sessions was improved to make the program more relevant to the actual needs of young people with depression, based on the subjects’ self-specific feelings and evaluations. The pre-experiment followed strictly to inclusion and exclusion criteria for the selection of subjects and was randomized to prevent cross-contamination between subjects. We found that all study participants cooperated positively with the study, were highly compliant and were able to successfully complete all training sessions without dangerous negative emotions or side effects, validating the reliability and safety of the training in this study. After the pre-experiment, social anxiety scores, social avoidance and distress mood decreased in the intervention group compared to the control group, while social self-efficacy scores increased relatively after the intervention, as detailed in Table 3.

**TABLE 3 T3:** The grading of the pre-experiment (n1 = n2 = 6; LASA, Liebowitz social anxiety scale; SAD, social avoidance and distress scale; PSSE, scale of perceived social self-efficacy; HAMD-17, Hamilton depression scale).

Entries	Before the trial		After the trial	
	Intervention group	Control group	Intervention group	Control group
LSAS	55.50 ± 21.20	52.25 ± 20.30	41.75 ± 17.21	51.50 ± 13.90
SAD	22.50 ± 3.64	22.25 ± 3.90	16.25 ± 5.31	22.00 ± 4.30
PSSE	52.2 ± 10.35	43.75 ± 4.66	54.50 ± 7.92	45.00 ± 7.45
HAMD-17	19.25 ± 1.75	19.50 ± 1.19	10.75 ± 1.48	11.50 ± 2.06

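### The planning effect (δ = 16.5) cannot be found in the pilot table it is said to come from, the stated inputs do not return 62, and seven pilot means do not fit six patients per arm

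*Protocol article*

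**What the plan says.** Under Official experiment, the protocol article names the LSAS as the primary outcome, prints a formula for comparing two means with a leading factor of 2², and sets error rates: "Take α = 0.05, β = 0.10". It does not say whether α is one- or two-sided. The two planning values are attributed to the pilot: "From the pre-test, we can calculate that σ2 = 243.04 and δ2 = 272.25". The result is given as "estimating a sample size of about 62 cases", raised by 20% to 74, that is "37 in the intervention group and 37 in the control group".

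The pilot is described under Preliminary experiments: "We included 12 young adults with depression, six in the intervention group and six in the control group". Its results are in Table 3 of the Discussion, whose caption also gives six per group. The LSAS row reads 55.50 ± 21.20 before and 41.75 ± 17.21 after in the intervention group, and 52.25 ± 20.30 before and 51.50 ± 13.90 after in the control group.

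**The concern.** The sample size for the primary outcome depends on δ and σ, and the article says that both come from the pilot. A reader who takes the square root of 272.25 and turns to Table 3 does not find 16.5, and cannot reach 62 from the printed formula either. The means themselves then look incompatible with the stated number of pilot patients.

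At stake is the justification of the trial's size. If the effect that the pilot supports is smaller than 16.5, the power differs from what the stated inputs imply, and the reader cannot tell which contrast the trial was sized for. If the table does not describe six patients per arm, σ and any replacement δ are also in doubt.

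**Working it through.** **Inputs.** From Official experiment: α = 0.05, β = 0.10, σ² = 243.04 (σ = 15.59), δ² = 272.25 (δ = 16.5), N = 62 before dropout. From Table 3: the four LSAS means and SDs above.

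**1. The plan's own figure.** The formula is n = 4(z_α + z_β)²σ²/δ². For two equal arms this is the total; the per-arm number has a factor of 2 in place of 4.

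- Two-sided: (1.960 + 1.282)² = 10.507, and 4 × 10.507 × 243.04 / 272.25 = 37.5, so 38 in total (19 per arm).
- One-sided: (1.645 + 1.282)² = 8.564, and 4 × 8.564 × 243.04 / 272.25 = 30.6, so 31 in total.

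Neither is 62. Two routes do reach it:

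- take the one-sided total of 31 as a per-arm number and double it; or
- use δ = 13.0 two-sided: 2 × 10.507 × 243.04 / 169.00 = 30.2, so 31 per arm and 62 in total.

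The article does not show which, if either, was used.

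**2. Is δ in Table 3?**

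| LSAS contrast | Calculation | Value |
|---|---|---|
| Between groups, after | 51.50 − 41.75 | 9.75 |
| Difference in change | 13.75 − 0.75 | 13.00 |
| Change, intervention | 55.50 − 41.75 | 13.75 |
| Change, control | 52.25 − 51.50 | 0.75 |
| Between groups, before | 55.50 − 52.25 | 3.25 |

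None is 16.5, which is 27% above 13.00 (16.5/13.00 = 1.27) and 69% above 9.75 (16.5/9.75 = 1.69). The variance nearly matches: the pooled after-trial value is (17.21² + 13.90²)/2 = 244.70, against 243.04. So δ is the planning value that is out of line.

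**3. Do the means fit n = 6?** The LSAS total is a sum of whole-number items ("The final scores are added together, and the higher the total score, the more severe the social anxiety state"), and the other three scales are described as item-scored too. A mean of six totals, multiplied by 6, must therefore be a whole number up to rounding.

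| Scale | Mean | × 6 |
|---|---|---|
| LSAS | 52.25 | 313.5 |
| LSAS | 41.75 | 250.5 |
| SAD | 22.25 | 133.5 |
| SAD | 16.25 | 97.5 |
| PSSE | 43.75 | 262.5 |
| HAMD-17 | 19.25 | 115.5 |
| HAMD-17 | 10.75 | 64.5 |

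Seven of 16 means fail; the other nine are attainable. The failing 41.75 enters both treatment contrasts, 9.75 and 13.00.

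**4. Power.** Two-sample t-test (noncentral t), two-sided α = 0.05, SD 15.59, individual-level:

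| δ | 31 per arm | 37 per arm | Total needed for 90% (formula) |
|---|---|---|---|
| 9.75 | 68% | 76% | 108 |
| 13.0 | 90% | 94% | 62 |
| 16.5 | 98% | 99% | 38 |

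The 13.0 row assumes that 15.59 is also the SD of change. The article does not report that SD.

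**The case against.** The strongest defence is that 62 may well be adequate. It exceeds the 38 that the stated δ needs two-sided, and it is what a difference in change of 13.0 requires at SD 15.59. The Abstract describes the primary outcome as a change from baseline, and the planned repeated-measures analysis considers an intervention-by-time interaction, so 13.0 is arguably a more relevant contrast than 9.75, which ignores a baseline difference of 3.25. This stands. A reader might infer that the trial is underpowered, or that 90% power is unattainable; the documents do not support that. A shortfall at SD 15.59 follows only if 9.75 is the target.

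Nor does the pilot refute 16.5 as a planning assumption. Taking Table 3 at face value with six per arm, the 95% interval around 9.75 is 9.75 ± 2.228 × 9.03, about −10 to 30. The fault is that 16.5 is presented as calculated from the pilot.

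A reader might also infer from the means that pilot patients were dropped. The means would fit four or eight per arm (PSSE 52.2 only if it is 52.25 cut to one decimal), but when the SDs are checked as well, none of 4, 6 or 8 reproduces every mean and SD pair. The baseline HAMD-17 SD of 1.19, for example, fits none of the three. Missing scores, another n and transcription error all remain possible. The Discussion's statement that "all study participants cooperated positively with the study, were highly compliant and were able to successfully complete all training sessions" does not settle it: it concerns training sessions, which the pilot controls did not receive, and not completed questionnaires.

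Finally, it can be said that Table 3 should not serve as a benchmark if it is itself in doubt. That is fair. The values 9.75 and 13.00 show that the printed figures disagree; they are not offered as reliable effects.

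**Conclusion.** The sample size justification is wrong as written, in three respects:

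- δ = 16.5 does not follow from the pilot data shown;
- the stated formula and inputs give 38 or 31 in total, not 62;
- seven of 16 pilot means do not fit the stated six per arm.

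At 31 per arm, power runs from 68% to 98% according to which δ is meant, so the stated inputs do not support the claimed 90%. It is not shown that 62 is too few, or that pilot patients were left out.

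The first two points rest on arithmetic with printed figures. The third assumes whole-number totals with complete items and no imputation, as the scale descriptions imply. The power figures assume SD 15.59, two-sided α and independent patients; allocation is by ward, and they make no allowance for that.

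**What to change.** 1. Re-tabulate Table 3 from the 12 pilot records and give the true n for each cell, with a reason wherever it is not six.
2. Replace δ² by the value that the corrected table supports and name the contrast. On the present table this would be 9.75² = 95.06 for after-trial scores or 13.00² = 169.00 for difference in change. Pair it with the matching SD: the SD of change if the difference in change is used.
3. State whether α is one- or two-sided and whether the formula's n is total or per arm, and show the calculation that leads to the planned number.
4. Restate the power at 62 evaluable patients (74 enrolled), and say that it ignores allocation by ward.

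The cost is re-tabulating 12 records and rewriting one paragraph. The stated power may become less favourable.
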